### Outcomes and Measurements

#### Primary and Secondary Outcomes

Our primary outcome will be self-reported diagnostic confidence as measured by response to the survey question in the postvisit questionnaire that asks participants after reviewing the collective intelligence output for cases randomized to the intervention group: “How confident do you feel about your diagnosis for this patient?” (Not at all, somewhat, moderately, and very). We chose this outcome based on previous literature in diagnostic safety suggesting that diagnostic confidence plays an important role in medical management, evolves over time in the process of making a diagnosis, and the ability to move diagnostic confidence may contribute to avoiding diagnostic error [18,19]. Furthermore, our preliminary studies for the proposed trial suggested that clinicians’ confidence in their clinical assessment is an important factor in their cognitive process for decision making and future approach to similar cases. We also chose this measure because it is likely the most sensitive to the impact of the collective intelligence on clinicians’ complex diagnostic decision-making process, whereas clinical outcomes such as *time to diagnosis* and diagnostic accuracy can be confounded by external health care system factors such as time to receive test results, financial incentives for diagnostic testing, and other factors. The secondary outcome will be *time to diagnosis*, defined as the interval between the time of the clinic visit from which a case with diagnostic uncertainty was identified for entry into the collective intelligence platform and the time at which the clinician will have established a diagnosis for that symptom or sign. We will ascertain the time of established diagnosis as the time at which the clinician documents the new diagnosis, the result for a confirmatory diagnostic testing becomes available, or empiric treatment was initiated. We will choose the earliest occurrence of any of these three events as the time of established diagnosis.

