### Analysis Plan

#### Primary Outcome

We will perform a bivariate logistic regression with the intervention status (clinician access to collective intelligence output vs no access to collective intelligence) as the predictor and diagnostic confidence as the outcome, clustering on clinician. Self-reported diagnostic confidence will be treated as a categorical variable with “not at all” as the reference group.

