#### Multiple Hypothesis Testing

We will report the results of the hypothesis test for the primary outcome without adjustment for multiple hypothesis testing. No formal penalization for multiple hypothesis testing is planned for the secondary, subgroup, or exploratory outcome analyses, as we will treat them as exploratory and hypothesis generating. We will report 95% CIs for all point estimates.

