#### Sample Size Justification

We planned our sample size using the primary outcome of clinician confidence in diagnosis, rated on a case-by-case basis. We anticipated an ability to detect (with 80% power) a 20% difference in clinicians rating their confidence in the case diagnosis as somewhat or very high, when comparing cases with versus without collective intelligence feedback. Assuming clustering of confidence ratings within clinicians at *r*=.3, we estimated that we need 33 clinicians with about 20 cases in total (10 with collective intelligence and 10 without collective intelligence; n=660 total cases).

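### The primary analysis of the four-level confidence scale names no single test, and the sample size is set on a binary split that this analysis does not use

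*Protocol article*

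**What the plan says.** All four places are in the Protocol article.

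- **Primary and Secondary Outcomes:** the primary outcome is one question with four answers in rising order, "Not at all, somewhat, moderately, and very".
- **Analysis Plan, Primary Outcome:** "We will perform a bivariate logistic regression with the intervention status" as predictor, clustered on clinician. On coding: "Self-reported diagnostic confidence will be treated as a categorical variable", with *not at all* as the reference level. No ordering, cut-point or joint test is given.
- **Multiple Hypothesis Testing:** "We will report the results of the hypothesis test for the primary outcome without adjustment for multiple hypothesis testing". The test is in the singular.
- **Sample Size Justification:** the target, at 80% power, is "a 20% difference in clinicians rating their confidence in the case diagnosis as somewhat or very high". The correlation within clinician is 0.3, and the result is 33 clinicians with about 20 cases each, half per arm, 660 in all.

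**The concern.** Four statements about one endpoint should lead to one comparison, and these do not. A four-level outcome with a reference level yields three odds ratios for arm: *somewhat*, *moderately* and *very*, each against *not at all*. If none is named in advance as the primary test, the result can be declared from whichever is significant. The coding also ignores the ordering of the answers, so the analysis does not ask directly whether confidence rose.

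The sample size concerns something else: a yes/no share made of the second and fourth levels without the third. A reader cannot tell whether the authors meant *moderately or very* or *somewhat or higher*, which are different endpoints. Neither is what the primary model estimates.

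**Working it through.** **1. Can 660 be reproduced?** From the protocol: a 20% difference, 80% power, r = 0.3, 10 cases per arm per clinician. Not stated: control rate, alpha, sidedness. Assumed: two-sided 5%, in line with the planned 95% intervals, and 20% read as percentage points.

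Pooled two-proportion formula at 25% vs 45% (mean 0.35):

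n = [1.96·√(2·0.35·0.65) + 0.8416·√(0.25·0.75 + 0.45·0.55)]² / 0.20² = (1.322 + 0.555)² / 0.04 ≈ 88.1, so 89 per arm.

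Design effect 1 + (10 − 1)·0.3 = 3.7. Total 2 × 89 × 3.7 ≈ 659 cases, and 659/20 ≈ 33 clinicians. By symmetry 55% vs 75% gives the same. Other control rates from 5% to 75% give 363 to 718 cases. So 660 fits a binary comparison under one choice of unstated inputs.

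**2. Does the literal split measure confidence?** Assume control shares of 10/40/35/15% (lowest to highest level) and one common odds ratio of 2.333, which moves *moderately or very* from 50% to 70%.

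- At least *somewhat*: odds 9 × 2.333 = 21, so 95.45%.
- At least *moderately*: odds 1 × 2.333, so 70.0%.
- *Very*: odds 0.1765 × 2.333 = 0.4118, so 29.17%.

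Intervention shares are therefore 4.55/25.45/40.83/29.17%. *Somewhat* plus *very* is 40 + 15 = 55.0% under control and 25.45 + 29.17 = 54.6% under intervention. A large rise in confidence leaves the split as worded almost unchanged.

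**3. What do the three contrasts give for the same shift?** Odds ratios against *not at all*:

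- *somewhat*: (25.45/4.55)/(40/10) = 1.40
- *moderately*: (40.83/4.55)/(35/10) ≈ 2.57
- *very*: (29.17/4.55)/(15/10) ≈ 4.28

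One shift yields three different answers, so it matters which is called primary.

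**4. Error and power by simulation.** Set-up: 33 clinicians × 20 cases, latent intraclass correlation 0.3, clinician-jackknife standard errors on 32 df, 1,500 trials per setting. A rank-based generalised odds ratio stood in for the proportional-odds test. Control distributions are assumed.

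| Control shares (%) | Common OR | Any of three contrasts | 3-df test | One ordinal test |
|---|---|---|---|---|
| 5/25/40/30 | 1.5 | 26% | 52% | 74% |
| 10/30/35/25 | 1.5 | 52% | 55% | 76% |
| 5/25/40/30 | 1.65 | 35% | 70% | 88% |

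A separate 600-trial run of the first row gave 28%, 47% and 72%. Further runs put the 3-df test at 50–56% and the ordinal test at about 75%. In the first row *moderately or very* moves only from 70.0% to 76.4%. Across settings, an odds ratio of 1.5 is a 6- to 8-point shift.

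With no effect, at least one contrast was significant in 6.6% and 9.0% of trials with *not at all* at 5–10%, and in about 7–12% across all runs. Three independent tests would give 1 − 0.95³ = 14.3%. The 3-df test held its level (4–5%).

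**5. At the 20-point target.** With *moderately or very* moving from 70% to 90% (control 5/25/40/30%), the ordinal and 3-df tests both reach about 100%, and any-of-three at least about 94%. The reason is that arms are compared within clinician, where the variance factor is nearer 1 − 0.3 = 0.7 than 3.7.

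**The case against.** Five points can fairly be made for the plan.

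- **A joint test exists.** A multinomial model with one binary predictor has a standard 3-df test of arm. It fits the singular wording, and an analysis plan not shown here may name it. This stands: the defect is that no test is named, not that none can be derived. The conflict between the coded outcome and the powered outcome remains, because the article states both.
- **The word multinomial does not appear.** Correct. It is the natural reading of a four-level outcome with a reference group, but it is a reading.
- **The power loss is small at the target.** This stands. A reader might infer from the odds-ratio 1.5 figures that the trial is underpowered. Those figures concern effects about a third of the planned difference.
- **Rarity of *not at all* is assumed.** Cases are chosen for diagnostic uncertainty, so this answer may be common. With 20% in that level and log odds ratio 0.41, any-of-three power was 72% against 79% for the ordinal test. The weakness of single contrasts therefore depends on the unknown distribution.
- **Ordinal modelling is partly a choice.** The output could unsettle some clinicians and reassure others, and a common odds ratio could average that away. This supports keeping level-specific results in the report. It is no reason to leave the primary test unnamed.

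**Conclusion.** The point holds as an inconsistency and an unnamed test. The primary analysis, read as multinomial, yields three contrasts with none designated, and the 80% power statement refers to a binary share that this analysis does not use and that matches no contiguous cut of the scale.

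The cost is a null error of about 7–12% if any significant contrast is accepted. For shifts of 6 to 8 points, power is about 50–56% with a 3-df test where an ordinal test has about 75%. At the 20-point target there is no material loss. The gain from the fix is one directional, prespecified test with better precision for smaller effects, not a rescue of the trial's power.

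Two further inferences are not supported. The total of 660 is not shown to be wrong: it can be matched for a binary endpoint. Nor can the sample-size phrase be taken to mean *moderately or very*, since *somewhat or higher* is an equally possible intention.

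All simulation figures rest on assumed control distributions and a common odds ratio. This should be fixed, but it does not invalidate the design.

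**What to change.** Before any arm-level data are analysed, and by dated amendment:

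1. Name one primary test. A cumulative-logit model with a clinician random intercept and one common odds ratio, tested once at two-sided 5%, is preferred.
2. Check proportional odds, and report level-specific results descriptively so that shifts in both directions stay visible.
3. Add one stated contiguous cut of the scale as the supportive binary analysis.
4. Have the sponsor state which cut was used for sizing, with its control rate and alpha, and correct the Sample Size Justification to match.

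No new data are needed. The costs are reliance on the proportional-odds summary, which items 2 and 3 offset, and a documented change after data collection, which the Results section reports as complete in June 2019.

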#### Secondary Outcome

We will use Cox regression to compare time-to-diagnosis (T2Dx) between the intervention versus the control cases (ie, intervention status as primary predictor and T2Dx as outcome).

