**Methods:**

This is a pragmatic randomized controlled trial of using collective intelligence in cases with diagnostic uncertainty from clinicians at primary care and urgent care clinics in 2 health care systems in San Francisco. Real-life cases, identified for having an element of diagnostic uncertainty, will be entered into a collective intelligence digital platform to acquire collective intelligence from at least 5 clinician *contributors* on the platform. Cases will be randomized to an intervention group (where clinicians will view the collective intelligence output) or control (where clinicians will not view the collective intelligence output). Clinicians will complete a postvisit questionnaire that assesses their diagnostic confidence for each case; in the intervention cases, clinicians will complete the questionnaire after reviewing the collective intelligence output for the case. Using logistic regression accounting for clinician clustering, we will compare the primary outcome of diagnostic confidence and the secondary outcome of *time with diagnosis* (the time it takes for a clinician to reach a diagnosis), for intervention versus control cases. We will also assess the usability and satisfaction with the digital tool using measures adapted from the Technology Acceptance Model and Net Promoter Score.

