#### Exploratory Analyses

We will perform mixed-effect multivariable logistic regressions to compare diagnostic confidence, T2Dx, and diagnostic accuracy of intervention versus control cases, accounting for clustering by clinician and adjusted for baseline diagnostic uncertainty, perceived case difficulty, patient age, race, gender, number of comorbid conditions, type of visit (new, returning, drop-in, or urgent care), and primary care clinician characteristics such as professional degree (NP vs MD), specialty (family vs internal medicine), and years of experience. We have chosen covariates a-priori based on clinical judgment. For cases randomized to the intervention, mixed-effect bivariate logistic regressions will compare physicians’ diagnostic accuracy before and after reviewing the collective intelligence, adjusted for the aforementioned clinician characteristics. We will use bivariate and multivariable linear regressions to compare the number of diagnostic testing and use logistic regressions to compare the occurrence of unexpected clinical visits at 30 days between intervention versus control cases.

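### The article names conflicting models for time to diagnosis, and its Cox sentence states no clinician term

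*Protocol article*

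**What the plan says.** Three places in the protocol article give a model for T2Dx.

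- Abstract, Methods: "Using logistic regression accounting for clinician clustering, we will compare the primary outcome of diagnostic confidence and the secondary outcome of" the time a clinician takes to reach a diagnosis.
- Analysis Plan, Secondary Outcome: "We will use Cox regression to compare time-to-diagnosis (T2Dx) between the intervention versus the control cases", with intervention status as the primary predictor. Clinician is not mentioned.
- The Exploratory Analyses section of the Analysis Plan: "mixed-effect multivariable logistic regressions to compare diagnostic confidence, T2Dx, and diagnostic accuracy of intervention versus control cases", with clinician clustering taken into account and further covariate adjustment.

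The outcome is "defined as the interval between the time of the clinic visit from which a case with diagnostic uncertainty was identified" and the time a diagnosis is established. For that end point: "We will choose the earliest occurrence of any of these three events as the time of established diagnosis". No cut-point turns the interval into a yes/no variable.

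The section just before the Cox sentence does name clustering for the primary outcome: "as the predictor and diagnostic confidence as the outcome, clustering on clinician". Under Selection, Entry, and Randomization of Clinical Cases, half of each clinician's cases go to each arm, in blocks of four.

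**The concern.** A logistic model needs a binary outcome. Without a cut-point, the abstract's analysis and the exploratory one cannot be run for T2Dx. Any cut-point chosen later discards timing and adds an unplanned choice. The Results section says that data collection is complete and analysis is still to come, so the model should not be left open.

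The Cox sentence has a second gap. Each clinician contributes about 20 cases, and randomisation is balanced within clinician. Differences between clinicians in how fast diagnoses are reached are therefore balanced between arms. A Cox model that leaves clinician out treats this variation as noise: its model-based standard error is too large and its hazard ratio lies closer to 1. What is at stake is power and interval width for the secondary outcome.

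**Working it through.** **Text check**

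| Place | Model for T2Dx | Clinician clustering | Runs as written? |
|---|---|---|---|
| Abstract, Methods | Logistic | Stated | No: no binary T2Dx |
| Secondary Outcome | Cox | Not stated | Yes |
| Exploratory Analyses | Mixed-effect logistic, adjusted | Stated | No: no binary T2Dx |

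The obvious cut-point, diagnosed by 6 months, may not help. The chart-review section excludes cases still uncertain after 6 months. If that applies to T2Dx, nearly every retained case would count as diagnosed.

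**Size of the clinician effect**

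The plan states no power, event count or clustering value for T2Dx, so there is no figure of its own to reproduce. The check is a simulation.

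Inputs from the documents:
- 33 clinicians × 20 cases = 660 (Sample Size Justification)
- 10 cases per arm within each clinician

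Assumed inputs:
- exponential times, with 70% of control cases diagnosed by 180 days and the rest censored
- normal clinician effect on the log hazard, SD 0.25, 0.5 or 0.8
- true within-clinician hazard ratio 1 or 1.25, the same for every clinician
- two-sided 5% tests, 2,000 trials per setting (Monte Carlo error about 1 point for power and 0.5 point for a 5% rate)

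For scale, the plan's r=.3 is for confidence ratings. If T2Dx clustered equally, SD = √(0.3/0.7 × π²/6) = √0.705 ≈ 0.84. Nothing in the article says that it does.

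| SD | Null rejection, no clinician term | Null rejection, stratified | Power at 1.25, no clinician term | Power at 1.25, stratified | Loss |
|---|---|---|---|---|---|
| 0.25 | 4.6% | 5.3% | 66.8% | 66.9% | 0.1 |
| 0.5 | 2.5% | 4.3% | 59.4% | 65.4% | 6.0 |
| 0.8 | 2.1% | 4.6% | 47.3% | 65.2% | 17.9 |

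At SD 0.8 under the null, the unstratified model's standard error averages 0.093, while its estimates have an SD of 0.079. At a true 1.25 it estimates 1.19, against 1.25 when stratified.

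Two other simulations in the same frame give:
- SD 0.5: 59% against 65% (6 points), and 57% against 66% (9 points)
- SD 0.8: 44% against 58% (14 points), and 44% against 63% (19 points from rounded figures)

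The 14-point result had fewer events: its standard error of 0.102 implies about 4/0.102² ≈ 384, against 0.7 × 660 = 462.

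**If unresolved cases are excluded**

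With cases undiagnosed at 180 days removed, power at a true 1.25 is 14.4% against 17.5% at SD 0.5 (3.1 points), and 13.6% against 23.1% at SD 0.8 (9.5 points). Both analyses then have little power, which is a separate matter.

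**If the effect varies between clinicians**

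Take a log hazard ratio with mean 0 and SD 0.3. At clinician SD 0.5 and 0.8, rejection is:
- no clinician term: 6.1% and 4.1%
- stratified, model-based standard error: 8.2% and 8.5%
- stratified, cluster-robust standard error with a t reference on 32 degrees of freedom: 4.6% and 5.1%

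**The case against.** The strongest reply is that the Cox sentence is silent on clustering and does not rule it out. It calls intervention status the primary predictor, which leaves room for other terms. The abstract and the exploratory section both attach clinician clustering to T2Dx. How clinician enters a Cox model is commonly left to a full analysis plan. This stands: a reader might infer that the plan abandons clustering for T2Dx, and the text does not show that. The conflict between logistic and Cox models remains, because a fuller plan that followed one statement would contradict another.

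It is also fair that the exploratory model is a separately labelled adjusted analysis, not a rival to the main one. But it still has no binary T2Dx to model.

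Other stronger readings also fail.

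- A reader might expect ignored clustering to inflate false positives, as in a cluster-randomised trial. Here randomisation is within clinician, and with a common effect the test is conservative.
- A reader might take the whole gap between 1.19 and 1.25 as bias. Part of it is non-collapsibility: a marginal and a within-clinician hazard ratio are different quantities.
- A reader might treat a large power loss as established. It rests on an assumed SD and vanishes at 0.25.
- A reader might also fault the linear model for the number of diagnostic tests. That outcome is exploratory, no distribution is given, and a linear model still estimates a difference in means. A count model would be a preference.

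**Conclusion.** The point holds as a conflict in the stated models: one outcome, two model families, and clustering stated in two places but not in the sentence that defines the main analysis. This needs no assumption beyond the text.

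The statistical consequence is conditional. If the Cox model is run with no clinician term and diagnosis times differ materially between clinicians, the test is conservative and power is lost. At a hazard ratio of 1.25 with about 30% censored, the loss runs from nil (SD 0.25) through 6 to 9 points (SD 0.5) to roughly 14 to 19 points (SD 0.8). The documents do not say where in that range the trial lies, and the figures differ if unresolved cases are excluded. The primary outcome is unaffected, and the plan treats secondary results as hypothesis generating. This should be corrected before analysis, but it does not threaten the trial's main conclusion.

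**What to change.** - State one main T2Dx analysis: Cox regression stratified by clinician, the unit within which cases are randomised, or Cox with a shared clinician frailty.
- For the adjusted version, use a Cox model with a clinician term. If it is stratified, clinician-level covariates such as degree or specialty cannot be estimated, so a frailty model suits it better.
- Remove T2Dx from the logistic sentences in the abstract and in Exploratory Analyses.
- State whether the exclusion of cases unresolved at 6 months applies to T2Dx or whether those cases are censored.
- Add a cluster-robust standard error as a sensitivity analysis, because the stratified model can reject somewhat too often if the effect varies between clinicians (about 8% in the check above).

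The cost is wording and a few lines of code. No new data are needed.

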#### Survey Analysis

We will use *t-* test statistics to describe the NPS and TAM score (overall and for each variable) by clinician characteristic (NP vs MD; years of practice; and specialty—internal vs family medicine).

#### Exploratory Analyses

We will perform mixed-effect multivariable logistic regressions to compare diagnostic confidence, T2Dx, and diagnostic accuracy of intervention versus control cases, accounting for clustering by clinician and adjusted for baseline diagnostic uncertainty, perceived case difficulty, patient age, race, gender, number of comorbid conditions, type of visit (new, returning, drop-in, or urgent care), and primary care clinician characteristics such as professional degree (NP vs MD), specialty (family vs internal medicine), and years of experience. We have chosen covariates a-priori based on clinical judgment. For cases randomized to the intervention, mixed-effect bivariate logistic regressions will compare physicians’ diagnostic accuracy before and after reviewing the collective intelligence, adjusted for the aforementioned clinician characteristics. We will use bivariate and multivariable linear regressions to compare the number of diagnostic testing and use logistic regressions to compare the occurrence of unexpected clinical visits at 30 days between intervention versus control cases.

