Collective intelligence is defined as shared or group intelligence that emerges from the collaboration or collective efforts of many individuals. It harnesses the ability of a group to outperform the individual in a variety of cognitive tasks [7]. IT platforms offer the opportunity to connect people and harness their collective intelligence through crowdsourcing—the practice of obtaining input into a task or project by enlisting the services of a large number of people via the internet [9]. In discrete tasks related to medical decision making, such as classification of radiology scans and pathological specimens, collective intelligence technology has been shown to improve accuracy when compared with individual decision making [10,11]. However, the impact of collective intelligence technology on diagnostic accuracy remains unproven in outpatient practice. Studies examining collective intelligence technologies have shown that users are enthusiastic about cross-discipline collaboration and easily obtaining expert feedback but wary of inaccuracies and inefficiency of using a collective intelligence tool [12].

In previous simulation testing, the collectively derived output from a collective intelligence platform outperformed its individual physicians in identifying the correct diagnosis in its assessment of standardized clinical cases [13,14]. However, effective implementation of such a tool in the outpatient setting requires examination of its efficacy and usability in real-world primary care and urgent care clinics.

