Once the collective intelligence output becomes available for a case, the study team randomizes it to the intervention or control cases. The study team assigned each case a unique study identification number for tracking purposes. Using a random number generator in blocks of four, we will randomize half of the cases, for each clinician, to an intervention group in which the clinician will receive a collective intelligence output between 60 and 80 hours from the time the clinician saw the patient in the clinic (ie, within 24-36 hours of case entry). For cases randomized to the controlled group, Human Dx will generate collective intelligence, but it will not be shared with the clinician. Clinicians will complete an online postvisit questionnaire for all of their cases (control and intervention) that provides their initial impressions of the case (eg, differential diagnosis and perceived case difficulty) and level of diagnostic confidence. The questionnaire for cases assigned to the intervention group includes additional questions that the clinician will answer after reviewing the collective intelligence output to assess the effect of the output on their diagnosis, plan, and confidence. The study scribes and the *contributors* on Human Dx will be blinded to case randomization.

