#### Exploratory Clinical Outcomes

We will measure and analyze specified, additional outcomes that are relevant to the diagnostic process. We will define diagnostic accuracy as having the correct diagnosis listed in the top 3 answers of the collective intelligence output (for intervention cases) or in the top 3 of the clinician’s list of possible diagnoses collected via survey data (for control cases). In addition, we will measure the number of diagnostic tests related to the initial complaint, ordered by the clinician within 30 and 90 days of the case presentation, and the number of unexpected visits (drop-in, urgent care, or emergency room) related to the initial presentation within 14 and 30 days of the index visit. Unexpected visits have been associated with higher risk of diagnostic error [1]. We refer to these as exploratory outcomes because we expect them to be highly variable both within and between clinicians and do not know whether we will have the statistical power to analyze them. Descriptive analyses of these outcomes may generate hypotheses for future study.

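### As stated, the exploratory before-after accuracy comparison ignores case pairing and shows only net change, and its accuracy definition must be reconciled with the outcome section

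*Protocol article*

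**What the plan says.** The comparison is in the protocol article, Analysis Plan, Exploratory Analyses. It is restricted to intervention cases, its method is a mixed-effect logistic model with the two time points as predictor, and its target is given as "diagnostic accuracy before and after reviewing the collective intelligence, adjusted for the aforementioned clinician characteristics". The opening sentence of that section, on the models that compare intervention with control cases, names clustering by clinician. The before-after sentence does not spell out its random effects, and no clustering by case is mentioned anywhere.

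The outcome is defined under Exploratory Clinical Outcomes. A case counts as accurate on "having the correct diagnosis listed in the top 3 answers of the collective intelligence output (for intervention cases") or, in the other group, "in the top 3 of the clinician’s list of possible diagnoses collected via survey data (for control cases").

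The data behind a before-after comparison are described under Selection, Entry, and Randomization of Clinical Cases. For every case the questionnaire "provides their initial impressions of the case (eg, differential diagnosis and perceived case difficulty) and level of diagnostic confidence". For intervention cases there are further questions, answered "after reviewing the collective intelligence output to assess the effect of the output on their diagnosis, plan, and confidence". The Postvisit Questionnaires section tells participants to record their initial thinking before opening the output. The chart review section has two investigators establish the final diagnosis at 6 months and excludes cases that are still uncertain.

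**The concern.** Each intervention case supplies a pair: the clinician's diagnosis before and after seeing the output, both judged against the same final diagnosis. The two directions of change mean opposite things. Wrong to right is a benefit, and right to wrong is an error that followed exposure to the tool. A model that links observations only through the clinician treats the two halves of a pair like any two of that clinician's cases. Its odds ratio then depends on the proportions correct before and after, so corrections and spoiled diagnoses offset each other. The planned covariates cannot help, because clinician characteristics are identical in both halves of a pair.

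The Background section reports that users of such tools are "wary of inaccuracies and inefficiency of using a collective intelligence tool", so the right-to-wrong rate is something readers of this trial will look for. No stated analysis reports it.

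The accuracy definition adds a second difficulty. If it is carried into the before-after analysis, the after value describes the output and not the clinician.

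**Working it through.** **Inputs from the document.** Sample Size Justification: 33 clinicians, about 20 cases each, half with the output. 33 x 20 = 660 cases, of which 33 x 10 = 330 are intervention cases. The document gives no figure for the before-after analysis, so there is none to reproduce.

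**Assumed inputs.** 50% correct before review (165 of 330) and the switch counts below. Both are illustrations only.

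**1. Same net change, different harm.** Let b be the number corrected and c the number spoiled.
- Scenario A: b = 17, c = 0. Correct after review: 165 + 17 - 0 = 182.
- Scenario B: b = 50, c = 33. Correct after review: 165 + 50 - 33 = 182.

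Both give 182/330 = 55.2%, a net gain of 17/330 = 5.2 points.

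**2. Unpaired odds ratio** (pairing ignored, between-clinician variance taken as zero for simplicity).
- OR = (182/148) / (165/165) = 1.23.
- SE(ln OR) = sqrt(1/182 + 1/148 + 1/165 + 1/165) = 0.156.
- 95% CI = exp(0.207 ± 1.96 x 0.156) = 0.91 to 1.67; p = 0.19.

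Estimate, interval and p value are identical in A and B.

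**3. Paired analysis of the same data.** The SE of the change is sqrt[((b + c)/N - ((b - c)/N)^2)/N].
- A: sqrt[(17/330 - 0.0515^2)/330] = 1.2 points; exact McNemar p<0.0001.
- B: sqrt[(83/330 - 0.0515^2)/330] = 2.7 points; exact McNemar p = 0.08.
- Unpaired, both: sqrt[(0.5 x 0.5 + 0.552 x 0.448)/330] = 3.9 points.

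Pairing distinguishes the scenarios and is more precise in both.

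**4. Check with fitted models.** 330 pairs in 33 clinicians, 50% correct before review, marginal (GEE) and clinician-random-effect logistic models:

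| Corrected / spoiled | Spoiled, % of 330 | Marginal OR | Clinician-random-effect OR |
|---|---|---|---|
| 16 / 16 | 5 | 1.00 | 1.00 |
| 49 / 49 | 15 | 1.00 | 1.00 |
| 33 / 0 | 0 | 1.50 | 1.55 |
| 66 / 33 | 10 | 1.50 | 1.52 |
| 82 / 49 | 15 | 1.50 | 1.51 |

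For a 10-point net gain, anything from 0 to 49 spoiled cases gives practically the same estimate.

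**5. What the right-to-wrong proportion would show.** Treating cases as independent, B gives 33/330 = 10% (95% CI about 7% to 14%). A gives 0/330 with an exact upper limit of about 1.1%. These intervals are too narrow. Suppose the within-clinician correlation of 0.3, which the article gives for confidence ratings, also applied to switches. The design effect would be 1 + (10 - 1) x 0.3 = 3.7 and the effective number 330/3.7 = 89. The intervals become roughly 5% to 18% for B, and an upper limit near 4% for A (1 - 0.025^(1/89)). Excluding cases still uncertain at 6 months, and non-response, would widen them further.

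**6. The definition, set beside the analysis.** Exploratory Clinical Outcomes scores an intervention case on the output's top 3. Exploratory Analyses speaks of the physicians' accuracy before and after. If the first governs the second, the after value is fixed by the output whatever the clinician concluded, and the right-to-wrong cell no longer describes clinicians changing their minds.

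**The case against.** A reader might infer that harm from the output is never measured in this trial. The documents do not support that. The initial differential, post-review questions that cover the diagnosis, and an adjudicated final diagnosis are all to be collected case by case. The outcome section also foresees descriptive analyses of the exploratory outcomes. What is missing is a stated plan to count the two directions of change. A condensed article may leave a cross-tabulation to a fuller document, so the absence of a table would not by itself be a finding. What remains is the analysis the article does state.

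A reader might also infer that the plan could not possibly tell the two scenarios apart. That depends on the random effects, which are not spelled out for this comparison. With a case-level effect the estimate would move towards the discordant ratio: 50/33 = 1.52 in B, unbounded in A. That is a fair point and is why the conclusion is conditional. But the article names clustering only by clinician, and a ratio still does not give the harm rate: 66/33 and 20/10 both equal 2.0, while the spoiled share is 33/330 = 10% in one and 10/330 = 3% in the other.

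Other objections stand in part. Accuracy is exploratory and no multiplicity-controlled claim rests on it. The Discussion leaves the impact on accuracy and harm to larger studies. Right to wrong on a top-3 scale may mean only that the correct diagnosis slipped to fourth place. Unexpected visits, compared between randomized groups, are a harm-oriented proxy, though they too show only a net difference. These points limit the weight of the concern but do not answer it.

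**Conclusion.** The point holds for an exploratory analysis. Read with clustering by clinician only, the stated model discards the pairing, estimates net change, and leaves the right-to-wrong rate unreported. In the illustration, 0 and 33 spoiled cases out of 330 give the same odds ratio of 1.23, with an unpaired standard error of 3.9 points against 1.2 or 2.7 for the paired analysis. The switch counts and the 50% starting accuracy are assumptions; the document gives no accuracy rate, so the size of any real effect is unknown. Separately, the definition of accuracy for intervention cases and the before-after comparison of physicians' accuracy do not fit together and must be reconciled. Neither point affects the primary or secondary outcome.

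**What to change.** - State that, for this analysis, accuracy is scored on the clinician's own top-3 list both before and after review, and reconcile Exploratory Clinical Outcomes with it. This presumes that the postvisit questionnaire elicits a revised list. The instrument is in Multimedia Appendix 1, which is not shown, so that needs confirming first.
- Report the paired 2x2 table (right-right, wrong-right, right-wrong, wrong-wrong), with the right-to-wrong and wrong-to-right proportions and 95% CIs that allow for clustering by clinician. Give the number of cases excluded for persistent uncertainty or missing responses.
- Use a case-paired comparison: McNemar-type allowing for clinician, conditional logistic regression, or a random effect for case nested in clinician. Do not present the net odds ratio alone.
- Label all of this exploratory.

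The cost is one table and a few sentences in the analysis plan. No further data are needed if the questionnaire already records a revised list. If it does not, the before-after analysis of the clinicians' own accuracy cannot be done as described, and the report should say so.
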